### **Group B: Standard (non technological) care intervention**

For the standard care group, participants will receive a total of 8 sessions of standard (non-technological) visual training over a 4 week period. As there is currently no accepted “gold standard” visual training approach for use in PwP, the control methodology for this study has been adapted from control conditions used in previous vision therapy trials and traditional therapy practice. Participants will undergo 20 minutes of visual training drills involving a variety of visuo-motor and perceptual tasks (primary pen and paper), followed by a further 10 minutes of games requiring hand-eye coordination skills (e.g. Jenga, throwing and catching). More details of the procedures can be found in *Appendix 19*.

### **OUTCOMES**

For the purposes of this study, feasibility will be explored in relation to safety and acceptability of the TVT intervention. See *Appendix 20* for full description of feasibility outcomes for the study.

To estimate the potential effects of TVT in PwP, a set of clinical outcomes relevant to PwP will be assessed. The primary clinical outcome will be change in visual attention from baseline to follow-up assessed with the Trail Making Test and the Senaptec Sensory Station.

Secondary clinical outcomes will be changes in balance and gait, mobility, physical endurance, quality of life, cognition and falls-efficacy. Gait and balance characteristics will be recorded via wearable

sensors (e.g. accelerometers) used during standing and walking under different conditions (including but not limited to single and dual tasks). Spatiotemporal gait characteristics (e.g., gait speed (m/s), variability (CV%), step/stride length (m), stride time (s), swing time (%), asymmetry, and step width (cm)) will be determined. Balance characteristics will include sway area (mm^2), sway path length (mm) and sway velocity (mm/s).

Additional measures will be used to describe the characteristics of the participants in terms of disease status, multimorbidity and mood.

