## **Research aims**

The aims of this study are to

1. Assess the feasibility of a technological visual training (TVT) intervention that requires wearing stroboscopic glasses and use of a tablet application in PwP
2. Measure the potential effects of TVT on visual function in PwP to determine if it produces greater benefit than standard (non-technological) care and assess the feasibility of a future large full-scale study.

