#### ***Trail Making Test (TMT) Parts A and B (Appendix 7)***

The Trail Making Test is a visual attention assessment that has been used within various neurological and cognitively impaired groups since the 1940s. The test is done in two parts; A and B. The patient is

asked to draw lines to consecutively numbered circles on one work sheet (Part A) and then to connect the same number of consecutively numbered and lettered circles on a separate work sheet, alternating between the two sequences (Part B). Subjects are told to work quickly and not to deviate from the appropriate sequence. The examiners test the subjects and record the time, in seconds, needed to complete each part of the test. Any errors are counted and corrected by the examiner, with the timer still going during correction time.

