### ***Senaptec Sensory Station (SSS), (Appendix 1)***

Visual and sensorimotor skills will be assessed on the Sensory Station which is a training station with a 50" screen. The SSS collects and analyses data relating to 10 sensory parameters (visual clarity/ contrast sensitivity/ depth perception/ near-far quickness/ perception span/ multiple object tracking/ reaction time/ target capture/ eye-hand coordination/ go-no-go).

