## **SAMPLE SIZE**

The Consolidated Standards of Reporting Trials Group and bodies such as The National Institute for Health Research state that not all studies need a power-based sample size calculation but they do all need a sample size justification [69]. As highlighted previously, this is a pilot study designed to test trial procedures and processes and to get estimates of parameters for a main trial sample size calculation. While we would hope to see trends in outcomes, the study is not designed to give a formal assessment of efficacy and there are few examples of visual training studies in PwP with which to base a sample size on. The majority of visual training and SVT studies have used relatively small cohorts (n<20), but have found statistically significant differences with intervention. Therefore, we propose recruiting a cohort of 40 participants (20 participants in each arm of the study) for the purposes of this study.

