## **Statistical Analysis**

Statistical analysis will be undertaken using SPSS (v.26, IBM). All statistical tests will be carried out at the 5% two-sided level of significance. Demographic characteristics and baseline data will be summarized using descriptive statistics, including means, standard deviations, median, minimum, maximum and inter-quartile ranges for continuous or ordinal data and percentages for categorical data. The descriptive statistics will be tabulated and presented graphically for clarity.

The statistical methods to be used are outlined in the following paragraphs;

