### **Efficacy Analysis**

***Aim 2: What are the potential effects of technological visual training in PwP and how do they compare to standard visual training techniques?***

The main focus of this aim of the study is to determine how the two treatments (TVT and standard care) influence participant outcomes over time, particularly visuomotor performance.

For this aim, data for the primary efficacy outcome (TMT) and secondary outcomes (balance, gait etc.) will be analysed using repeated measures analysis of covariance (ANCOVA), comparing the pre-intervention to post-intervention outcome. The dependent variable will be the outcome of interest (i.e., TMT), with age, gender, disease duration and H&Y stage as covariates. In case of any missing data, sensitivity analysis (last observation carried forward) will be used with delta-adjusting imputation.

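### The primary clinical outcome is two instruments in OUTCOMES and the Trail Making Test alone in Efficacy Analysis, and neither section names one score, leaving between 2 and 12 candidates, each tested at 5%

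*Protocol*

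**What the plan says.** In OUTCOMES, the primary clinical outcome is "change in visual attention from baseline to follow-up assessed with the Trail Making Test and the Senaptec Sensory Station". In Efficacy Analysis, the plan refers to "data for the primary efficacy outcome (TMT) and secondary outcomes (balance, gait etc", with the parenthesis going on to close the list of secondary outcomes. It then adds: "The dependent variable will be the outcome of interest (i.e., TMT", again with no other instrument named. The Sensory Station does not appear in that section.

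The TMT section describes two parts and has examiners "record the time, in seconds, needed to complete each part of the test", so the test produces two scores. The Sensory Station section states: "The SSS collects and analyses data relating to 10 sensory parameters". The parameters listed there range from visual clarity and contrast sensitivity to multiple object tracking and go-no-go.

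Statistical Analysis sets one rule for everything: "All statistical tests will be carried out at the 5% two-sided level of significance". The protocol gives no hierarchy, composite or adjustment. SAMPLE SIZE says that "the study is not designed to give a formal assessment of efficacy", while the second research aim is to measure potential effects "to determine if it produces greater benefit than standard (non-technological) care".

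**The concern.** The two definitions cannot both be followed. On one, a result on the Sensory Station is a primary result; on the other, it is not. Because no score is named within either instrument, the choice of what to call primary stays open until results exist. The Blinding section says investigators cannot be kept blind, so that choice could be made by people who know which arm it favours.

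Which instrument is primary is not a neutral question here. Several Sensory Station parameters (eye-hand coordination, go-no-go, multiple object tracking, depth perception) share names with app drills listed for the experimental arm in Appendix 18, while the control arm works mainly with pen and paper. Improvement on the Sensory Station could partly reflect practice on similar tasks.

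Two things are at stake. One is the false-positive rate of whatever is reported as the primary clinical finding. The other is the pilot's stated purpose of supplying parameter estimates for a main-trial sample size, which needs one defined score with one standard deviation.

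**Working it through.** The protocol states no familywise error rate or power, and its sample size of 40 comes from no formula, so there is no figure of its own to reproduce.

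**Inputs**
- TMT scores: 2, one time for each part (TMT section).
- Sensory Station scores: 10 (Sensory Station section).
- Level: 5% two-sided for each test (Statistical Analysis).
- Correlation between scores: not given. It is assumed below and varied.

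**Number of candidate scores**
- Efficacy Analysis reading, TMT only: 2.
- OUTCOMES reading, both instruments: 2 + m, where m is the number of Sensory Station parameters that count as visual attention. The protocol does not give m. It lies between 1 and 10, so the total lies between 3 and 12.
- Overall range: 2 to 12. Derived scores such as Part B minus Part A are not counted, because the protocol names none.

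**Chance of at least one false-positive result among k independent tests, no true effect**

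P = 1 − (1 − 0.05)^k

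- k = 1: 0.050
- k = 2: 1 − 0.95² = 0.0975
- k = 3: 1 − 0.95³ = 0.143
- k = 12: 1 − 0.95¹² = 0.460

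**Allowing for correlation**

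Scores on the same person will be correlated. For a common correlation ρ, 200,000 sets of test statistics were simulated as x_j = √ρ·c + √(1 − ρ)·e_j, with c and e_j standard normal, counting sets in which any |x_j| exceeds 1.96.

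| Assumed ρ | k = 2 | k = 12 |
|---|---|---|
| 0 | 0.097 | 0.460 |
| 0.3 | 0.095 | 0.397 |
| 0.5 | 0.091 | 0.321 |
| 0.7 | 0.082 | 0.233 |
| 0.9 | 0.071 | 0.134 |

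Every entry exceeds 0.05. The calculation needs only that each test holds its own 5% level, so it does not depend on the details of the planned repeated measures ANCOVA.

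**After the fix**

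One named score gives 0.050. Reconciling both sections to the TMT without naming a part still leaves k = 2, or 0.0975 if independent. If all 12 were kept as primary, a Bonferroni level would be 0.05/12 = 0.0042 for each.

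**The case against.** The strongest reply is that this is a pilot. Feasibility is the first aim, the sample size rests on no endpoint, and SAMPLE SIZE disclaims a formal efficacy assessment. Nothing in the protocol makes p < 0.05 on a clinical outcome a criterion of success or a condition for the main trial. That stands, and it lowers the severity. It does not remove the point, because the plan still labels an outcome primary and tests it at 5%.

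A second reply is that choosing a TMT part, selecting Sensory Station parameters and setting a multiplicity rule can be left to a statistical analysis plan that is not shown here. That is fair for those details. It does not cover the conflict itself: an analysis plan could not follow both sections of the protocol.

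Third, 12 is a ceiling. OUTCOMES limits the outcome to visual attention, and visual clarity, contrast sensitivity and depth perception are not evident attention measures. Efficacy Analysis, the section that sets out the model, implies only two candidates. This also stands, so a reader who takes 46% as the error rate of the trial goes beyond the documents.

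A reader might also infer that, with 20 per arm, a null result would wrongly be taken as no benefit. The documents do not support that step. They announce no such conclusion, and the opening of the second aim, OUTCOMES and Efficacy Analysis all speak of measuring or estimating potential effects. A power figure from an unadjusted two-sample test would not describe the planned analysis either, and low power has no bearing on which outcome is primary.

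**Conclusion.** The point holds as a contradiction in the current text. OUTCOMES and Efficacy Analysis define different primary clinical outcomes, and neither identifies one score. On either reading, the chance of a false-positive primary result exceeds the nominal 5%: 9.8% for two independent scores, up to 46% for twelve, and about 32% or 23% for twelve at an assumed correlation of 0.5 or 0.7. These figures assume no true effect, unadjusted tests at 5%, and freedom to report any candidate score as primary. The true count is undefined within 2 to 12 because the protocol does not say which Sensory Station parameters measure visual attention.

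This should be fixed. It does not threaten the feasibility aim or the conduct of the trial. The wording of the second aim is a minor side issue, since the surrounding text is already framed as estimation.

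**What to change.** Before any data are seen by arm, amend OUTCOMES and Efficacy Analysis so that both name the same single primary score. One TMT part would agree with Efficacy Analysis as it stands. The investigators could settle the conflict differently, provided that both sections match and one score is named. Label the other TMT part and the Sensory Station parameters as secondary or exploratory, and report them as between-arm differences with 95% confidence intervals. If more than one primary score is wanted, list them and state the multiplicity adjustment.

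Optionally, reword the second aim from determining greater benefit to estimating the difference between arms, in line with SAMPLE SIZE.

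The cost is a wording amendment; visits, data collection and sample size do not change. The downside for the investigators is that the headline can no longer rest on whichever score looks best.

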## **SAMPLE SIZE**

The Consolidated Standards of Reporting Trials Group and bodies such as The National Institute for Health Research state that not all studies need a power-based sample size calculation but they do all need a sample size justification [69]. As highlighted previously, this is a pilot study designed to test trial procedures and processes and to get estimates of parameters for a main trial sample size calculation. While we would hope to see trends in outcomes, the study is not designed to give a formal assessment of efficacy and there are few examples of visual training studies in PwP with which to base a sample size on. The majority of visual training and SVT studies have used relatively small cohorts (n<20), but have found statistically significant differences with intervention. Therefore, we propose recruiting a cohort of 40 participants (20 participants in each arm of the study) for the purposes of this study.

## **Data Analysis**

The subjects or observations to be excluded, and the reason for their exclusion will be documented and approved by those responsible, prior to statistical analysis. Any exclusion documentation will be stored together with the remaining study documentation.

## **Blinding**

Due to the pilot nature of this project and limited research personnel involved, it will not be possible to ensure blinding of investigators. Blinding will not be possible for participants, but they will be asked to refrain from mentioning the nature of the intervention they receive (technology versus standard) to the assessors in the Clinical Gait Laboratory.

## **Statistical Analysis**

Statistical analysis will be undertaken using SPSS (v.26, IBM). All statistical tests will be carried out at the 5% two-sided level of significance. Demographic characteristics and baseline data will be summarized using descriptive statistics, including means, standard deviations, median, minimum, maximum and inter-quartile ranges for continuous or ordinal data and percentages for categorical data. The descriptive statistics will be tabulated and presented graphically for clarity.

The statistical methods to be used are outlined in the following paragraphs;

### **Feasibility and Safety Analysis**

***Aim 1: Is a technological visual training intervention (using a combination of stroboscopic glasses and a tablet application) feasible, safe and acceptable for use in a Parkinson's population?***

Data will be presented as mean +/- standard deviation (normally distributed data) or median (interquartile range). Differences between the standard care and TVT group will be compared by two-tailed t-test (e.g. mean duration of visual training undertaken at each one hour visit), or chi-square test (e.g. total number of differences in adverse events between arms, compliance/adherence).

Feasibility outcomes will also be reported both descriptively and narratively in relation to usability and acceptability of the TVT package (see *Appendix 20*).

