## **METHODS**

---

**TRIAL DESIGN:** A 4-week, single-site, parallel group, pilot RCT (allocation ration: 1:1)

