The effects of using technology such as stroboscopic glasses as part of a visual training intervention in PwP is not yet known. Commonly recognised effects of prolonged exposure to strobe lighting such as that generated by flickering fluorescent lighting include headaches and eye fatigue, nausea and photosensitive epilepsy. Although participants will only be using the strobe glasses for up to 10 minutes at a time (including breaks), the eligibility criteria for this study has been designed to ensure that individuals who have a history of conditions that are known to be triggered by flashing/strobe lights (such as epilepsy or migraine) will be excluded from the study. Participants will also be given the opportunity to trial the strobe glasses prior to commencing procedures to ensure they can be tolerated. A qualified physiotherapist from the study team will always be with the participant whilst the technology is being used to monitor user-experience and ensure adequate rest periods are taken.

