## Appendix 20 – Feasibility Outcomes

| Outcome              | Description                                                           | Analysis                                                                                                         |
|----------------------|-----------------------------------------------------------------------|------------------------------------------------------------------------------------------------------------------|
| Safety               | Adverse events (mild, moderate, or severe) caused by the intervention | Total number; compare differences in adverse events between the 2 arms.                                          |
| Amount               | Duration of actual visual training undertaken during each visit       | Compare average duration of visual training tolerated during each one hour visit [min]                           |
| Compliance/adherence | Rate of scheduled and completed sessions                              | Total n sessions completed /total n sessions scheduled (%)                                                       |
| Acceptability        | Motivation

Useability                                          | Pittsburg Rehabilitation Participation Scale Scores (compare mean scores between arms)
System Usability Scale |
| Equipment            | Function of mobile technology in participants' homes                  | Number of issues with equipment, such as break downs, shortage of equipment, internet access                     |

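### The between-arm test of adverse events cannot show that TVT is safe, as Aim 1 asks, and the protocol gives no interval, margin or acceptable rate to answer that question

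*Protocol*

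**What the plan says.** In the protocol's Feasibility and Safety Analysis section, Aim 1 asks whether the intervention is "feasible, safe and acceptable for use in a Parkinson's population". Between-arm differences are to be examined by t-test (for example, training time per visit) or by "chi-square test (e.g. total number of differences in adverse events between arms, compliance/adherence").

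The Safety row of Appendix 20 gives the analysis as "Total number; compare differences in adverse events between the 2 arms". The Statistical Analysis section adds: "All statistical tests will be carried out at the 5% two-sided level of significance". The Sample Size section proposes "recruiting a cohort of 40 participants (20 participants in each arm of the study"), and says the number is not based on power.

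None of these places states an acceptable event rate, a margin or a confidence interval for safety. The extra descriptive and narrative reporting promised under Aim 1 is tied to usability and acceptability. The Sample Size section disclaims a formal assessment of efficacy and gives no matching caution for safety.

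**The concern.** A test of difference takes equal event rates as its null hypothesis. Rejecting that null shows that the arms differ. Failing to reject it shows only that the data were insufficient to separate them. Whether TVT is safe is a question about how high its event rate, or its excess over control, could plausibly be. An estimate with an upper limit, or a comparison with a stated margin, answers that. A p-value above 0.05 does not.

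Safety is one of this pilot's main products. The Outcomes section explores feasibility through safety and acceptability, and the Safety Considerations section says: "The effects of using technology such as stroboscopic glasses as part of a visual training intervention in PwP is not yet known". The result will inform the decision on a full-scale trial. With no other criterion on the page, a non-significant test could be taken as the answer to Aim 1 even when a several-fold excess of events remains compatible with the data.

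**Working it through.** **Inputs from the protocol.** 20 per arm, 1:1 allocation (Sample Size, Methods); chi-square test (Feasibility and Safety Analysis); two-sided 5% (Statistical Analysis). The protocol states no power or event rate for safety, so there is no figure to reproduce.

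**Assumptions.** Each participant is counted once (at least one event or none). Control rates of 0% to 30% are used to show a range. There is no dropout unless stated.

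**The test.** With x of n affected on control and y of n on TVT, s = x + y and N = 2n, the uncorrected statistic is

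X² = N·(x(n−y) − y(n−x))² / (n²·s·(N−s)), significant if above 3.84.

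Smallest significant splits at n = 20:

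- 0 v 4: 40·80²/(400·4·36) = 4.44. At 0 v 3 it is 3.24.
- 1 v 6: 40·100²/(400·7·33) = 4.33. At 1 v 5 it is 3.14.
- 2 v 8: 40·120²/(400·10·30) = 4.80. At 2 v 7 it is 3.58.

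So with one control participant affected, TVT needs 6 of 20 (30%) for significance; with two, it needs 8 of 20 (40%).

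**Chance of detection.** Sum the product of the two binomial probabilities over all significant splits. Corrected and exact versions are shown because expected cell counts are small (at 1 v 6, only 3.5 affected expected per arm).

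| Control v TVT | Uncorrected detects | Uncorrected misses | Yates detects | Fisher detects |
|---|---|---|---|---|
| 5% v 15% | 15.4% | 84.6% | 3.3% | 7.0% |
| 5% v 20% | 29.2% | 70.8% | 10.5% | 16.8% |
| 5% v 25% | 44.4% | 55.6% | 22.7% | 29.9% |
| 5% v 30% | 59.1% | 40.9% | 38.1% | 44.6% |
| 10% v 30% | 35.7% | 64.3% | 21.9% | 24.2% |
| 10% v 40% | 62.3% | 37.7% | 47.7% | 49.2% |
| 10% v 50% | 83.8% | 16.2% | 72.6% | 74.2% |
| 20% v 40% | 29.1% | 70.9% | 17.6% | 19.2% |
| 30% v 60% | 46.3% | 53.7% | 32.4% | 34.7% |
| 0% v 20% | 58.9% | 41.1% | 19.6% | 37.0% |

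The last row can be checked by hand. With no control events, significance needs at least 4 of 20 on TVT, and P(Binomial(20, 0.2) ≥ 4) = 1 − 0.411 = 0.589.

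If 10% drop out (18 v 18), uncorrected detection falls to 25.1% for 5% v 20% and 31.7% for 10% v 30%.

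**Size needed for 80% power.** Normal approximation, with p̄ the mean of the two rates and q = 1 − p:

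n = [1.96·√(2p̄q̄) + 0.842·√(p₁q₁ + p₂q₂)]² / (p₂ − p₁)²

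- 5% v 20%: (0.917 + 0.383)²/0.0225 ≈ 75.1, so 76 per arm.
- 10% v 30%: (1.109 + 0.461)²/0.04 ≈ 61.6, so 62 per arm.

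**What estimation would say.** The exact one-sided 95% upper bound for x of 20 is the 95th percentile of Beta(x+1, 20−x). For x = 0 this is 1 − 0.05^(1/20) = 13.9%; for x = 1 it is 21.6%; for x = 2 it is 28.3%. For a split of 2 v 2, a simple Wald 95% interval for the risk difference is 0 ± 1.96·√(2·0.1·0.9/20), or about ±19 percentage points.

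**The case against.** The strongest reply is that the protocol never says a non-significant test means TVT is safe. That is correct. A reader might infer that rule from a yes/no aim paired with a 5% test, but the text says only that the arms will be compared, and no conclusion or progression decision is tied to the p-value.

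Nor does safety rest on the test alone. Appendix 20 also reports the total number of events and grades their severity, sessions are supervised with a running log, and the Adverse Events section sets out recording and follow-up. The tests in the Aim 1 section are introduced as examples, the Outcomes section speaks of exploring feasibility, and the sample size is openly not power-based. Interval methods could also sit in a statistical analysis plan that is not at hand.

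Two further overstatements should be avoided. A reader might infer that the test can only count against TVT, but it is two-sided and can show fewer events on TVT as well as more. A reader might also infer that it usually misses any large excess. The table does not support that: with the uncorrected test, 0% v 20%, 5% v 30%, 10% v 40% and 10% v 50% are all detected more often than not.

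What remains is the mismatch between question and method. The protocol itself chooses a difference test as its inferential analysis for a question such a test cannot answer favourably. The counts carry no criterion or interval, and the caution about formal assessment covers efficacy only. That is a matter of what the protocol fixes, not of detail left for later.

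**Conclusion.** The point holds in limited form. The inferential safety analysis in the Aim 1 section and Appendix 20 is a difference test from which safety cannot be concluded, and a non-significant result could be misread because nothing else is set against which to judge the event rate.

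Under the assumed rates, with participants as the unit and the uncorrected chi-square, three- to fivefold excesses at control rates of 5% to 10% are missed in 56% to 85% of trials (5% v 15%, 20% and 25%; 10% v 30%). Yates or Fisher versions miss more. Larger excesses are mostly detected by the uncorrected test. The rates are illustrations, since the protocol supplies none. The argument that non-significance is not evidence of safety does not depend on them.

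This should be corrected, but it does not threaten the trial's conduct or the data collected.

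**What to change.** Amend the Feasibility and Safety Analysis section and the Safety row of Appendix 20 so that estimation carries the safety statement:

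- Report, per arm, the number and proportion of participants with at least one adverse event, and with at least one serious adverse event.
- Give an exact one-sided 95% upper confidence bound for the TVT proportion, and the TVT-minus-control risk difference with a 95% confidence interval.
- Give between-arm differences with 95% confidence intervals for tolerated training duration and for the Pittsburgh Rehabilitation Participation Scale.
- State that a non-significant between-arm test is not evidence of safety or of equal tolerability, and that the conclusion will name the largest TVT event rate the data do not exclude. Keep the chi-square and t-tests as descriptive only.

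This costs wording and no new data or participants. It also suits the pilot's stated purpose of estimating parameters for a main trial. The drawback is a less favourable statement: even with no TVT participant affected, the report would have to say that a rate of about 14% is not excluded.

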### **Group A: Technological Visual Training (TVT)**

The experimental group will receive a total of 8 sessions of TVT over a 4 week period. Each session will last up to 60 min of which 20 mins will be dedicated to a series of visual training drills using a mobile tablet device (see *Appendix 18* for list of training drills), and a further 10 mins will be spent doing simple hand-eye co-ordination activities (e.g. throwing and catching) whilst wearing stroboscopic glasses. The remaining time will be factored in for rest periods as required. Activities will be supervised at all times by the researcher who will keep a running log of issues that may arise during the intervention period such as adverse events, changes in medication or any environmental factors that could affect participant engagement or performance.

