#### **Adverse Events:**

Any untoward medical occurrence, unintended disease or injury or any untoward clinical signs in participants whether or not related to the intervention will be recorded as an adverse event and managed according to the Health Research Authority (HRA) Guidance (see *Appendix 21* for a description of adverse events taken from HRA Guidance).

Any serious adverse event (SAE) occurring to a research participant will be reported to the main Research Ethics Committee if the event is related to the administration of the research procedures and unexpected.

Recording of adverse events will start from the signature of the informed consent until the participant has completed or passed through the Day 7  $\pm$  1 days follow-up window. Information and assessments relating to the adverse event will be recorded in the adverse event section of the Case Report Form as per HRA Guidance and will be monitored until resolution or stabilization.

In the unlikely event of any serious adverse event occurring during this study, the University will be informed immediately (and no later than 72 hours after first awareness of the research team) and a written report provided. The university (acting as the Local Sponsor) will follow local reporting guidelines.

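### Chi-square tests on pooled sessions and total adverse events treat repeated observations within a participant as independent, and the safety comparison is described as limited to events attributed to the intervention

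*Protocol*

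**What the plan says.** Feasibility and Safety Analysis (Aim 1) says the arms will be compared with a "chi-square test (e.g. total number of differences in adverse events between arms, compliance/adherence". Statistical Analysis sets the level: "All statistical tests will be carried out at the 5% two-sided level of significance".

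Appendix 20 says what is compared. Adherence is "Total n sessions completed /total n sessions scheduled", as a percentage. The safety outcome is described as "Adverse events (mild, moderate, or severe) caused by the intervention", and its analysis column asks for a total compared between the two arms.

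The trial plans "40 participants (20 participants in each arm of the study". Each person has eight scheduled sessions: "The experimental group will receive a total of 8 sessions of TVT over a 4 week period" in Group A, and in Group B "participants will receive a total of 8 sessions of standard (non-technological) visual training over a 4 week period".

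The Adverse Events section is broader than Appendix 20: any untoward occurrence "whether or not related to the intervention will be recorded as an adverse event". The Blinding section says that blinding of investigators cannot be ensured.

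**The concern.** The participant is randomised, but the quantities tested are sessions and events, and each participant can contribute several. A Pearson chi-square on these totals assumes they are independent. A person who stops early misses a run of sessions. Someone who gets eye fatigue or nausea from the equipment may get it again. Positive correlation of this kind makes the chi-square standard error too small, so differences between arms look firmer than 20 people per arm can support. Feasibility and safety are Aim 1 and inform the case for a larger trial.

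The second issue is which events are compared. If only events attributed to the intervention count, the numerator depends on a causality judgement that may be made knowing the arm.

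**Working it through.** **No stated figure to reproduce.** The protocol gives no error rate, intraclass correlation (ICC), event rate, overdispersion or numerical adherence; Recruitment only expects compliance to be high. The values below are therefore assumptions, shown as ranges. With independent sessions or events, the Pearson test gives 0.049 to 0.051 in simulation, which is the nominal level.

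**Sessions.** Inputs: 20 participants per arm (Sample Size) and 8 sessions each (Groups A and B), so 20 × 8 = 160 per arm. The design effect is DE = 1 + (8 − 1) × ICC. The actual two-sided error is 2 × [1 − Φ(1.96/√DE)]. The simulation columns are beta-binomial, 50,000 runs, 90% adherence.

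| Assumed ICC | DE | Formula | Pearson, simulated | Yates, simulated |
|---|---|---|---|---|
| 0 | 1.00 | 0.050 | 0.050 | 0.030 |
| 0.05 | 1.35 | 0.092 | 0.092 | 0.063 |
| 0.1 | 1.70 | 0.133 | 0.133 | 0.097 |
| 0.3 | 3.10 | 0.266 | 0.269 | 0.223 |
| 0.5 | 4.50 | 0.356 | 0.366 | 0.318 |

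At 80% and 95% adherence the Pearson results are similar (0.269 and 0.271 at ICC 0.3).

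**Events.** With equal arms, the chi-square on totals a and b is (a − b)²/(a + b). If the variance of a person's count is V times its mean, the error is about 2 × [1 − Φ(1.96/√V)].
- V = 1.5: 1.96/1.225 = 1.60, giving about 0.11 (simulated 0.108).
- V = 2: 1.96/1.414 = 1.39, giving about 0.166 (simulated 0.164 to 0.168).
- V = 3: 1.96/1.732 = 1.13, giving about 0.26 (simulated 0.257 to 0.259).

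**One participant, with no ICC assumed.** Suppose one person stops after the first session, all 39 others complete, and all eight sessions count as scheduled. Missed sessions are 7/160 v 0/160.
- Difference = 7/160 = 0.04375; pooled proportion = 7/320 = 0.021875.
- Variance = 0.021875 × 0.978125 × (2/160) = 0.000267.
- Chi-square = 0.04375²/0.000267 = 7.16, p = 0.007 (Yates p = 0.022).
- By participant, the same data are 1/20 v 0/20 incomplete: Fisher p = 1.0, and rank-sum on sessions completed p = 0.34.

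For events, one person with a symptom at all eight sessions and no other events in the trial gives 8 v 0: (8 − 0)²/(8 + 0) = 8, p = 0.005.

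**When one dropout is not enough.** Let one person miss all 8 sessions.
- Completed 148 v 156 (other arm 156/160 = 97.5%): p = 0.040.
- Completed 147 v 155 (155/160 = 96.9%): p = 0.052.
- Completed 137 v 144 (144/160 = 90%): p = 0.23.

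**After the change of unit.** A t-test on each participant's completion proportion has simulated error of 0.040 to 0.051 at 80% to 90% adherence for ICC 0 to 0.7. At 95% adherence it falls from 0.048 to 0.016, which is conservative. A chi-square on participants with at least one event gives 0.042 to 0.054, except near 0 when almost everyone has an event.

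**Which events.** Appendix 20's description column restricts safety to caused events. Its analysis column and the Aim 1 text carry no such limit, and the Adverse Events section records everything. The document does not settle which events enter the comparison.

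**The case against.** The strongest defence is that the unit is never stated outright. The Aim 1 text gives examples only, its wording on adverse events is unclear, and the ratio in Appendix 20 could be computed per person. A statistical analysis plan, not shown here, could settle this. Part of that stands, but the protocol itself names both the test and the quantity, and a chi-square on a ratio of totals is most naturally read as pooled.

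Four stronger readings are tempting, and the documents do not support them.
- A reader might infer a fixed inflation, such as three- to seven-fold. That needs a session ICC of about 0.12 to 0.49. Over ICC 0 to 1 the formula runs from 1 to 9.8 times nominal, and ICC 0.1 gives 2.7.
- A reader might infer that any single dropout creates significance. It does so only when adherence elsewhere is almost complete.
- A reader might infer that p above 0.05 will be taken as proof of safety. No section ties feasibility or safety to a p-value, and feasibility outcomes will also be reported descriptively and narratively.
- A reader might infer that the unblinded therapist decides causality, or that unrelated events are lost. The Group A section has the supervising researcher log adverse events, but no section says who judges cause, and all events are recorded.

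**Conclusion.** The point holds in a limited form. As written, the pooled chi-square tests are anti-conservative whenever sessions or events correlate positively within a participant. How far is conditional: for sessions, about 0.09 to 0.36 against a nominal 0.05 over ICC 0.05 to 0.5, and lower with Yates correction; for events, about 0.11 to 0.26 over variance/mean ratios 1.5 to 3. The one-person examples need no ICC, but they do need near-complete adherence, or no other events, in everyone else.

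The restriction to caused events affects the comparison, not data capture. With investigator blinding not ensured, a comparison limited to attributed events is open to judgement that differs by arm, and the sections need reconciling.

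This should be fixed. It is not critical, because no stated decision rule turns on these tests.

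**What to change.** Reword Feasibility and Safety Analysis and Appendix 20 so that the participant is the unit.
- **Adherence:** each participant's sessions completed out of 8, compared by a participant-level test (rank-sum, permutation or t-test) with a 95% confidence interval for the difference. The choice among these is a matter of preference.
- **Safety:** the number of participants with at least one adverse event of any cause, by arm, with Fisher's exact test and a confidence interval. Show intervention-related events and total counts as further descriptive rows.
- **Aim 1 itself:** report the TVT-arm proportions with exact 95% confidence intervals. With 0/20 affected, the upper limit is 1 − 0.025^(1/20) = 16.8%, which tells the reader more than a p-value.
- **Consistency:** make Appendix 20 and the Adverse Events section agree on which events are compared.

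This needs no new data, only wording. The cost is wider intervals, and recurrence of events within a person is then shown only descriptively.
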